## Abstract

Fatigue is prevalent amongst people with long COVID, but is poorly understood. The sensory attenuation framework proposes that impairments in sensory processing lead to heightened perception of effort, driving fatigue. This study aims to investigate the role of somatosensory processing impairments in long COVID fatigue and quantify how sensory processing relates to other prominent symptoms of long COVID including autonomic dysfunction, mood and illness beliefs in driving the experience of fatigue. We will recruit 44 individuals with long COVID fatigue and 44 individuals with neither long COVID nor fatigue (controls). Our primary objective is to compare baseline somatosensory processing between individuals with long COVID fatigue and controls. Additionally, we will explore the associations between somatosensory processing, fatigability and the level of fatigue induced by cognitive and physical exertion. Due to the complex nature of fatigue, we will also investigate how long COVID, state fatigue, perceived effort, mood, illness beliefs, autonomic symptoms and autonomic nervous system function interact to predict trait fatigue. This comprehensive investigation aims to elucidate how sensory processing and other prominent symptoms interact to impact the experience of fatigue.

## INTRODUCTION

1

Long COVID is a multi‐system condition in which individuals experience persistent symptoms 12 weeks following acute COVID‐19 infection (Crook et al., 2021; National Institute for Health & Care Excellence, 2020). Fatigue is one of the most common and debilitating symptoms reported in long COVID (Joli et al., 2022), causing a significant impact on individuals, employers and healthcare systems (Townsend et al., 2020).

Fatigue is an experience of symptoms that can only be measured through self‐reporting. It is a complex phenomenon that is likely to involve overlap of physiological and psychological factors (Matura et al., 2018). Although difficult to define (Kluger et al., 2013), there has been recent consensus within another clinical condition that fatigue is a ‘range of symptoms from mild subjective feelings of tiredness to an overwhelming debilitating, and sustained sense of exhaustion that likely decreases one's ability to execute daily activities and function normally in family or social roles’ (Maxwell et al., 2024). In this study we use a multi‐framework approach to explore the complexity of potential mechanisms and drivers of long COVID fatigue. We specifically focus on the sensory attenuation model of fatigue, the role of autonomic dysfunction, the common‐sense model of self‐regulation, and the mood updating model to explore the complex interactions between physiological and psychological factors in long COVID fatigue.

The sensory attenuation model of fatigue (Kuppuswamy, 2022) proposes that impaired sensory processing increases effort perception, driving fatigue (de Doncker et al., 2018; Kuppuswamy, 2017). Somatosensory deficits exist across clinical conditions that involve fatigue (Jamali et al., 2017; Kessner et al., 2016), and somatosensory processing has been linked to fatigue (Ito et al., 2022). Sensory changes are common in long COVID (Trott et al., 2022), but the sensory attenuation model of fatigue has not been fully explored in this population.

There are two similar, but distinct, phenomena involved in somatosensory processing (Kilteni & Ehrsson, 2022). Attenuation is the suppression of somatosensory input that arises from one's own movement (reafferent input) in comparison to somatosensory input that arises from external sources (exafferent input). Gating is the suppression of externally generated somatosensory input during voluntary movement in comparison to when at rest. Somatosensory gating has been reported not to differ between individuals without long COVID and those reporting long COVID fatigue that had a moderate‐to‐severe impact on daily living (Baker et al., 2023). Previous studies in clinical conditions that experience fatigue have focused on somatosensory attenuation (Parthasharathy et al., 2022; Wolpe et al., 2018), but this has not been studied in long COVID. In this study we aim to replicate the Baker et al. (2023) finding that somatosensory gating is not different in individuals with and without long COVID fatigue, and extend this by asking whether somatosensory attenuation is different between individuals with and without long COVID fatigue (Research Question 1).

Fatigue can be considered as both a stable and enduring characteristic, reflecting how a person feels over weeks or months, and an instantaneous experience, reflecting how a person feels at a given moment. These concepts are referred to as trait and state fatigue, respectively. Although somatosensory processing has been studied in relation to trait fatigue (Baker et al., 2023; de Doncker et al., 2021), it is not well studied in relation to state fatigue. Definitions and measures of fatigue in long COVID cover different dimensions, such as physical, cognitive, emotional, psychosocial, and general fatigue and post exertional malaise ([name] et al., 2024 [Unpublished raw data]). It is unclear if different dimensions share the same underlying mechanisms. Here we focus on state fatigue in two of these dimensions—physical and cognitive. We will quantify relations between somatosensory processing and state fatigue induced by both a cognitive and a physical task (Research Question 2) and quantify how these are related to trait fatigue (Research Question 4). This will add to our understanding of the relations between and mechanisms underlying different dimensions of state fatigue and trait fatigue in long COVID.

The sensation of fatigue may be independent from objective measures of performance (Bailey et al., 2007; Krupp & Elkins, 2000; Lou et al., 2003). For example, Fietsam et al. (2023) found that individuals with long COVID reported more fatigue than individuals without long COVID but had similar levels of performance decline on an isokinetic fatigue task. The decline in an objective measure of performance over a discrete period of time is termed performance fatigability (Enoka et al., 2021). Understanding the association between fatigue and fatigability has been identified as an important goal for clinical research (Kluger et al., 2013). We will address this in our second research question by quantifying whether the change in performance over the cognitive and physical tasks (performance fatigability) is related to state fatigue induced by that task, whether this moderates the relation between somatosensory processing and state fatigue, and whether this is impacted by long COVID (Research Question 2).

In addition to understanding if somatosensory processing predicts fatigue, it is also of relevance to ask if fatigue impacts somatosensory processing (bidirectional arrows in Figure 1, blue boxes). This would potentially indicate that activities that increase fatigue and cause performance fatigability, could lead to disrupted somatosensory processing, further increasing the fatigue and fatigability. This will be addressed in our third research question, where we ask if the change in somatosensory attenuation (Research Question 3i) and somatosensory gating (Research Question 3ii) from pre‐ to post‐task is predicted by the change in state fatigue from pre to post task, fatigability during the task, population (long COVID/controls) and task (cognitive/physical).

**FIGURE 1 eph13615-fig-0001:**
[figure not shown]
Concept of interactions. Schematic illustration indicating the proposed relations between autonomic dysfunction, illness beliefs, mood (anxiety and depression) and somatosensory processing. We postulate that each of these factors (autonomic dysfunction, illness beliefs, mood) will impact fatigue via an impact on somatosensory processing. We also propose that fatigability and acute (state) changes in fatigue will have a bidirectional relation with somatosensory processing.

In conditions such as depression, autonomic dysfunction is a mediating factor in the experience of fatigue (Costa et al., 2023). Autonomic dysfunction is prevalent in long COVID (Dotan et al., 2022), potentially reflecting a disrupted balance between sympathetic and parasympathetic nervous systems (Jammoul et al., 2023). However, this has not yet been directly related to fatigue in this population. We propose that autonomic dysfunction may impact fatigue via an effect on somatosensory processing (Figure 1). No studies across any clinical conditions have explored the relations between autonomic dysfunction, somatosensory processing, and fatigue. This will be considered in Research Question 4 where we explore the role of the autonomic nervous system in trait fatigue. Additionally in exploratory analysis we will look at (i) the effect of autonomic dysfunction, on state fatigue via an effect on somatosensory processing, and (ii) the relations between autonomic dysfunction during exertion, state fatigue during exertion, and perceived effort during exertion.

The common‐sense model of self‐regulation (Leventhal et al., 2016) proposes that how an individual perceives their symptoms can be influenced by their mood, previous experiences, and beliefs. The mood updating model proposes that prior beliefs about the signals resulting from an action, as well as mood (particularly depression and anxiety), can impact perception of and response to stimuli (Clark & Watson, 2023). Depression and anxiety are a feature of long COVID (Fancourt et al., 2023), and the experience of long COVID symptoms has a profound impact on self‐identity and beliefs about illness (Callan et al., 2022). There is likely a complex interaction between illness beliefs, mood, perception of stimuli and symptom experience in long COVID that has not yet been explored. Understanding individual experiences driving symptom perception and response is essential for targeted interventions. These relations will be explored in Research Question 4, where we quantify if among individuals with long COVID, if trait fatigue is effected by the increase in state fatigue induced by a physical task, the increase in state fatigue induced by a cognitive task, mood, illness beliefs, autonomic symptoms and autonomic nervous system function.

## RESEARCH QUESTIONS

2

Research Question 1: Are pre‐task (baseline) somatosensory attenuation (Research Question 1a) and somatosensory gating (Research Question 1b) different between individuals with long COVID fatigue compared to controls?

Research Question 2: Is state fatigue following exertion predicted by somatosensory attenuation at baseline, somatosensory gating at baseline, the presence of long COVID (long COVID/controls), and the type of task (cognitive/physical), and is performance fatigability a moderator variable in this relation? State fatigue prior to exertion will be included as a covariate in this analysis.

Research Question 3: Is the change in somatosensory attenuation (Research Question 3a) and somatosensory gating (Research Question 3b) from pre‐ to post‐task predicted by the change in state fatigue during exertion, fatigability, the presence of long COVID (long COVID/controls), and the type of task (cognitive/physical)?

Research Question 4: Among individuals with long COVID, is trait fatigue predicted by the increase in state fatigue induced by a physical task, the increase in state fatigue induced by a cognitive task, mood, illness beliefs, autonomic symptoms and autonomic nervous system function?

This study will provide the first comprehensive investigation into the role of somatosensory processing in long COVID fatigue and explore how prominent symptoms in long COVID (autonomic dysfunction, altered mood, beliefs about the meaning of symptoms) interact with somatosensory processing, fatigability and the experience of fatigue.

## METHODS

3

### Ethical approval

3.1

Prior to recruitment of pilot participants, this study received ethical approval from Cardiff University School of Healthcare Sciences Research Ethics Committee (REC1160). The study conforms to the standards set by the *Declaration of Helsinki*, except for being registered in a publicly accessible database. This study will conduct experiments on humans, and written informed consent will be obtained from all participants.

### Participants and recruitment

3.2

Participants will be recruited via convenience sampling from the local community using passive recruitment methods (digital and physical posters and announcements). Recruitment will be targeted to match long COVID and control groups for age and gender. To be eligible, individuals must be between 18 and 69 years old. Somatosensory attenuation and gating change with age (Parthasharathy et al., 2022), particularly after the age of 69 years (Timar et al., 2023). This age group will therefore be excluded, to prevent age‐related effects on somatosensory attenuation and gating confounding the results. Participants must be able to speak and understand English and be able to provide informed consent. Participants will be excluded if they have any physical or psychiatric condition that would prohibit them from walking safely on a treadmill, taking part in a cognitive task or completing the full battery of assessments (Supporting information, Appendix 1).

For inclusion in the control group, individuals may have previously tested positive for COVID‐19 but must have been clear of all symptoms by 12 weeks following acute infection and must not report any ongoing fatigue. Participants in the control group must not report any underlying condition that interferes with their daily function. All inclusion and exclusion criteria will be evaluated by self‐report measurements (Supporting information, Appendix 1).

For inclusion in the long COVID group, individuals must self‐report a confirmed COVID infection (confirmed by positive lateral flow test or polymerase chain reaction test, or a clinical diagnosis) and report signs and symptoms that continued or developed 12 weeks or more after acute COVID‐19 infection (National Institute for Health & Care Excellence, 2020). As this study will focus on the impact of fatigue, individuals must report fatigue (physical, cognitive, mental, emotional, psychosocial fatigue or post‐exertional malaise) as one of their long COVID symptoms and must not have experienced any form of ongoing fatigue prior to COVID infection (Supporting information, Appendix 1).

### Experimental procedures

3.3

Prospective participants will be provided with a participant information sheet and an opportunity to ask questions. If they wish to participate, they will be directed to an online platform (JISC) and asked to fill in a consent form. Once informed consent has been provided, the participant will be contacted to schedule the two testing sessions.

A schematic illustration of the study timeline is shown in Figure 2. Prior to the testing sessions, participants will be directed to the online platform (JISC), which they are able to access from any place with internet connection to provide self‐reported measurements (Supporting information, Appendix 1) and complete a battery of validated measures (see ‘Outcome measures’). A contact email for the research team will be provided on every page of the online platform, in case of questions. Participants will be able to pause and restart this process multiple times. Pilot tests have indicated that this process will take 60 min in total.

**FIGURE 2 eph13615-fig-0002:**
[figure not shown]
Data collection timeline. HRV, heart rate variability. JISC is a digital platform designed specifically for education and research organizations that can be used for the creation and dissemination of surveys. BL, baseline; PRE‐1, immediately after pre‐task somatosensory gating measure; PRE‐2, immediately after pre‐task somatosensory attenuation measure; POST‐1, immediately after the completion of the task (cognitive or physical); POST‐2, immediately after post‐task somatosensory gating measure; POST‐3, immediately after post‐task somatosensory attenuation measure.

On completion of the participant characteristics and validated measures, participants will be given a unique, randomly generated four‐digit identifier. Consent forms, which will contain the participants personal details, will be saved separately from all other data and only identified with the participants four‐digit identifier.

The protocol is split into two testing sessions. Each session is expected to take up to 90 min. The two sessions are identical, except that in one session participants perform a cognitive task and in the other session they perform a physical task. Participants will be asked to complete both sessions in a crossover design. In each session, somatosensory processing (attenuation and gating) will be measured pre‐ and post‐task (physical or cognitive). The order of the two sessions will be randomized using the command randi([1 2]) in MATLAB software version 23.2 (MathWorks Inc., Natick, MA, USA), which will be run on the morning of the first testing session. A value of ‘1’ indicates that cognitive task will be performed first and ‘2’ indicates that the physical task will be performed first. Participants will be asked to return on a separate day for each session.

Upon arrival at each testing session, the participant will be re‐consented to ensure that they are still happy to participate and will then be prepared for data collection. The measure of somatosensory gating requires activity of the first dorsal interosseus muscle to be monitored in real time (see ‘Outcome measures’). To achieve this, the skin over the first dorsal interosseus muscle will be prepared using a mild abrasive gel (NuPrep, Weaver and company, Aurora, CO, USA) and a Trigno Quattro Sensor (Delsys Europe, Manchester, UK) will be placed over the muscle belly parallel to the radial border of the second metacarpal, just proximal to the junction between the muscle and distal tendon (Zijdewind et al., 1995). The reference sensor will be placed on the forearm. Heart rate will be measured in a similar way to ECG, using a surface electrode placed on the skin over the chest (Delsys Europe, Manchester, UK).

Pre‐task measures (somatosensory gating, somatosensory attenuation, state fatigue) will be evaluated (see ‘Outcome measures’ and Figure 2). Following this, the participant will be asked to perform the task (cognitive or physical, depending on the session). Immediately following the task, post‐task measures (somatosensory gating, somatosensory attenuation, state fatigue) will be evaluated (see ‘Outcome measures’ and Figure 2).

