##### Somatosensory attenuation

The somatosensory attenuation assessment is expected to take 10 min. Participants will be seated comfortably and positioned with their dominant hand placed on a table with their palm facing upwards. Participants will be given a practice trial to make sure they understand the task.

An audible beep will mark the start of the trial. The researcher ([name]) will press on the abductor pollicis brevis muscle of the dominant hand with a Digital Handheld Dynamometer (microFET2; Hoggan Scientific, Salt Lake City, UT, USA). The force will be applied through a digit transducer pad of 1 cm diameter to a magnitude of 4, 5, 6 or 7 N, and will be maintained for 3 s until a second beep marks the end of the 3 s. This constitutes an exafferent force. The magnitude of force applied is displayed in real time on the device and will be visible to the researcher, but not to the participant. After 2 s rest, a third beep will sound, and the participant will be asked to press the same probe onto the same section of skin with the same force that was exerted by the researcher with a second Digital Handheld Dynamometer (microFET2, Hoggan Scientific). This constitutes a reafferent force (Kilteni & Ehrsson, 2022).

Following a practice trial, each force level (4, 5, 6 or 7 N) will be performed eight times, for a total of 32 trials. These trials will be organized in two blocks of 16 trails. The force level will be randomized within MATLAB software. There will be an interval of 60 s between the two blocks. The average force across the 3 s is stored in the dynamometer for each trial and will be retrieved after the end of the session.

Somatosensory attenuation will be quantified as the mean force overcompensation between the exafferent force (generated by the researcher) and the reafferent force (generated by the participant). Mean force overcompensation will be calculated as the average difference between the exafferent and reafferent force (Wolpe et al., 2018), on each trial (*n* = 8) across each force level (*n* = 4). To examine force matching as a function of force level, the intercept and slope from the linear regression between exafferent and reafferent force will be calculated for each participant and condition. Example data are shown in Supporting information Figure S3, and the code used to calculate the outcome measure is provided as Supporting information.

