### Statistical analysis

3.7

A series of statistical analyses will be conducted to compare the descriptive characteristics of the two groups (long COVID/neither long COVID nor fatigue). The characteristics to be compared are age, gender, trait fatigue (FAS score, CFQ‐11 total score, CFQ‐11 physical subscale score, CFQ‐11 mental subscale score), impact of trait fatigue (MFIS physical subscale score, MFIS cognitive subscale score, MFIS psychosocial subscale score), mood (HADS‐A score, HADS‐D score), illness beliefs (BIPQ score), and autonomic symptoms (COMPASS‐31 score). Gender will be analysed as a categorical variable. A chi‐square test will be used to compare the gender distribution between the groups. All other variables will be analysed as ratio data and compared across groups using an independent samples if the data meet parametric assumptions (normality, verifying equal variance) and a Mann–Whitney *U* test if the data do not meet parametric assumptions.

Results will be summarized using a measure of central tendency (mean or median) and spread (standard deviation or interquartile range), test statistics, and *P*‐values for ratio data and frequency, percentage, chi‐square values, and *P*‐values for categorical variables.
Hypothesis 1Pre‐task (baseline) somatosensory attenuation will be different between individuals with long COVID fatigue and controls. We will also attempt to replicate the Baker et al. (2023) finding that somatosensory gating is not different between individuals with long COVID fatigue and controls. The independent variable will be ‘participants’, which consists of two categories: ‘individuals with long COVID fatigue’ and ‘controls’. The two dependent variables will be ‘somatosensory attenuation’ and ‘somatosensory gating’, measured at baseline during the first session participants attend.

This will be tested using a multivariate analysis of variance to test for an overall difference in somatosensory processing between populations, and to explore the differences in somatosensory gating and attenuation. We will check that the following assumptions are met: multivariate normality, independence and equal variance. If we find the multivariate analysis of variance is significant, we will conduct follow‐up univariate analysis of variance for somatosensory attenuation and somatosensory gating to identify specific contributions to the effect and will apply Bonferroni correction to control for the increased risk of Type I error.

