Hypothesis 2: State fatigue following exertion will be predicted by somatosensory attenuation at baseline, somatosensory gating at baseline, the presence of long COVID (long covid/controls), and the type of task (cognitive/physical). Performance fatigability will be considered a moderator variable in these relations. State fatigue prior to exertion will be included as a covariate in this analysis.

This will be tested using a linear mixed model:

$$Y_{ijk}=\mu +a_{i}+b_{j}+c_{k}+d_{ik}+e_{ik}+f_{ik}+g_{ijk}+\left(f_{ik}\times a_{i}\right)+\left(f_{ik}\times b_{j}\right)+\varepsilon_{ijk}$$
where:

*Y_ijk_
*: state fatigue following exertion in the *i*‐th group (long COVID/control) during task *j* (cognitive/physical) for the *k*‐th subject.μ: the overall mean of state fatigue following exertion.
*a_i_
*: the effect of the *i*‐th group (fixed effect: long COVID vs. control).
*b_j_
*: the effect of the *j*‐th task (fixed effect: cognitive vs. physical).
*d_ik_
*: the baseline somatosensory attenuation for the *k*‐th subject in the *i*‐th group.
*e_ik_
*: the baseline somatosensory gating for the *k*‐th subject in the *i‐*th group.
*f_ijk_
*: the performance fatigability for the *k*‐th subject in the *i*‐th group during the *j*‐th task.
*g_ijk_
*: the state fatigue prior to exertion for the *k*‐th subject in the *i*‐th group during the *j*‐th task (covariate).(*f_ik_
*×*a_i_
*): the interaction term between performance fatigability and group.(*f_ik_
*×*b_j_
*): the interaction term between performance fatigability and task.
*ϵ_ijk_
*: the residual error term, assumed to be normally distributed.
Hypothesis 3: The change in somatosensory attenuation (Research Question 3a) and somatosensory gating (Research Question 3b) from pre‐ to post‐task will be predicted by the change in state fatigue from pre to post, fatigability, the presence of long COVID (long COVID/controls), and the type of task (cognitive/physical).

We will use linear mixed models to test these hypotheses, with separate models for somatosensory attenuation and somatosensory gating:

$$Y_{ijk}=a_{i}+b_{j}+c_{ijk}+d_{ijk}+u_{0i}+\varepsilon_{ijk}$$
where:

*Y_ijk_
*: attenuation or gating at baseline in the *i*‐th group (long COVID/control) during task j (cognitive/physical) for the k‐th subject.
*a_i_
*: the fixed effect of the *i*‐th group (long COVID vs. control) on baseline attenuation.
*b_j_
*: the fixed effect of the *j*‐th task (cognitive vs. physical) on baseline attenuation.
*c_ijk_

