#### Planned exploratory analysis

3.7.1

Hypotheses 1, 2, 3 will be rerun with age included as a covariate.Hypotheses 1, 2, 3, 4 will be rerun with time of day (morning/afternoon) at which participants completed sessions and session order (cognitive/physical first) included as additional predictor variables.The effect of autonomic dysfunction during exertion, on state fatigue pre‐ to post‐exertion, via an effect on somatosensory processing post‐exertion will be tested using mediation analysis with separate models for somatosensory attenuation and somatosensory gating. This will be quantified in participants with and without long COVID.The relations between autonomic dysfunction during exertion, state fatigue during exertion, and perceived effort during exertion will be quantified in participants with and without long COVID during both tasks (cognitive/physical). This will be tested using correlation analysis.Test‐retest reliability will be conducted for each somatosensory processing measure (gating and attenuation), from the baseline measure from each session (cognitive/physical). This will provide a measure of whether somatosensory processing is stable over time.

We will carry out outcome neutral criteria that must be met for successful testing of the stated hypothesis. This includes checking for the absence of floor or ceiling effects. This will be done by examining data distributions to ensure that there are no extreme values that could impact the validity of results. Additionally, we will investigate the quality of the data and this will include frequency measures and the shape of the distribution.

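### Session order rests on one on-the-day randi([1 2]) call with no stated seeding; if MATLAB is reopened for each call, most or all participants could get the same order, confounding task with session

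*Protocol article*

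**What the plan says.** Section 3.3 (Experimental procedures) sets out a two-session within-person comparison of a cognitive and a physical task: "Participants will be asked to complete both sessions in a crossover design". It gives the allocation method as a literal command: "The order of the two sessions will be randomized using the command randi([1 2]) in MATLAB software version 23.2", "which will be run on the morning of the first testing session". The coding is also given: "A value of ‘1’ indicates that cognitive task will be performed first and ‘2’ indicates that the physical task will be performed first". The article mentions no seeding step, list prepared in advance, blocking or stratification by group.

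In section 3.7 the Hypothesis 2 model contains "task (fixed effect: cognitive vs. physical"), and the Hypothesis 3 models also have a fixed task effect. None of these models has a term for order or session. Order appears only in section 3.7.1, where the hypotheses are to be rerun with "session order (cognitive/physical first) included as additional predictor variables". The Hypothesis 1 outcomes are "measured at baseline during the first session participants attend".

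**The concern.** A crossover separates the task effect from first-versus-second-visit effects (familiarity, anticipation, after-effects of earlier exertion) only if some participants take each order. The method described draws one number at a time, on different days, and the article does not say what state the generator is in when each draw is made. If the software opens in the same state every time, a call made just after opening is not random: it repeats the same value.

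The task effects in Research Questions 2 and 3 are at stake. If everyone has the same order, physical versus cognitive is also first visit versus second visit, and no analysis of the collected data can tell the two apart. The planned rerun with order as a predictor would fail for the same reason, because the predictor would be constant.

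**Working it through.** **Inputs from the article.** The command, its timing and its coding are in section 3.3. Section 3.8 gives 44 per group, so 2 × 44 = 88 in total. Recruitment and data collection run from July 2024 to April 2025 (section 3.9).

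**The plan's own figure.** The article gives no figure for the order split, so only the sample size can be reproduced. For a standardised difference of 0.78 and two-sided alpha 0.05, the exact noncentral t calculation gives power 0.9469 at 43 per group and 0.9513 at 44. The stated 44 is right, and nothing below alters it.

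**Assumption, not in the article.** MATLAB opens with a Mersenne Twister generator in a fixed default state (seed 5489), and randi([1 2]) returns 1 + floor(2u), where u is the next uniform number.

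**Draws under that assumption.**
- u = 0.8147: 1 + floor(1.629) = 2
- u = 0.9058: 1 + floor(1.812) = 2
- u = 0.1270: 1 + floor(0.254) = 1
- u = 0.9134: 1 + floor(1.827) = 2

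The first ten draws are 2, 2, 1, 2, 2, 1, 1, 2, 2, 2.

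**Split over 88 participants, by number of order draws per MATLAB start.** With three per start, 29 full starts give 29 ones and 58 twos, and the 88th participant gets a 2. With four per start, 22 starts give 22 ones and 66 twos.

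Let *t* be the true physical-minus-cognitive effect and *s* the second-minus-first-session effect. A physical-first participant's difference has expectation *t* − *s*, and a cognitive-first participant's has *t* + *s*. Averaged without a session term, and leaving the covariates aside, the bias is *s*(nC − nP)/88. If a session term is added, the efficiency for *t* relative to an even split is 4·nC·nP/88².

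| Order draws per start | Cognitive first / physical first | Bias with no session term | Relative efficiency with a session term |
|---|---|---|---|
| 1 | 0 / 88 | −1.00 *s* | not estimable |
| 2 | 0 / 88 | −1.00 *s* | not estimable |
| 3 | 29 / 59 | −30/88 = −0.34 *s* | 6844/7744 = 0.88 |
| 4 | 22 / 66 | −44/88 = −0.50 *s* | 5808/7744 = 0.75 |
| Never restarted | 39 / 49 | −10/88 = −0.11 *s* | 7644/7744 = 0.99 |

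**Identifiability.** A design matrix with 88 participant columns plus task and session has 90 columns. With all orders the same its rank is 89, so task and session are fully aliased. With orders that vary at random its rank is 90.

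**Which row is plausible.** At most ten months for 88 first sessions is about 88/10 ≈ 9 a month, well under one per working day. One or two order draws per start is therefore realistic if MATLAB is closed between participants. The article does not say whether it is.

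**The case against.** The strongest reply is that the damaging premise lies outside the document. The article does not say what state MATLAB opens in, whether it is reopened before each call, or that no seeding command or start-up script is used. A condensed article may leave seeding to the scripts. This is correct, and it is why the point is conditional. It does not remove the point, because the article publishes the command, its timing and its coding as the procedure, and following those words exactly can yield a single order.

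A reader might infer that every participant will be physical first. The article does not support that. It would need a fresh start, no earlier random draw and at most two order draws per start. Section 3.4.7 says of another measure that "The force level will be randomized within MATLAB software", so other draws may advance the stream in an open session. The rows from 29/59 to 39/49 show the milder outcomes.

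Four further inferences also go too far:
- **Research Question 1 is compromised.** It is not. Its outcomes are taken before either task at the first visit, and a constant order does not alias group with session.
- **The test–retest analysis in section 3.7.1 is lost.** First- and second-session baselines can still be compared under a fixed order.
- **Repeated force-level sequences cause bias.** The article gives no command for these, each participant still receives eight trials at every level, and no harm can be shown.
- **Ordinary chance imbalance is a serious fault.** A 26:18 split in a group of 44 keeps 4 × 26 × 18/44² = 0.97 of the efficiency of 22:22. Properly seeded simple randomisation is legitimate.

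It is also fair to say that staff would probably notice a long run of the same result. That supports checking the counts, but the article does not build in such a check.

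**Conclusion.** The point holds as a conditional risk. The allocation method as written does not guarantee that session order varies. If MATLAB opens in its assumed default state, the result ranges from 0/88 (one or two order draws per start) to 39/49 (one continuous stream). At 0/88 the task effects in Research Questions 2 and 3 cannot be separated from session, and the exploratory order term cannot be estimated. At 29/59 or 22/66 the models as written would carry about a third to a half of any session effect into the task effect, though a session term could still separate them.

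The direction (physical first) and the exact splits depend on the assumed start state. The basic weakness does not: any fixed start state gives the same first draw after each opening. Under true randomisation, 88 identical orders would have probability 2 × 0.5^88 ≈ 6 × 10⁻²⁷, so the realised counts would settle the extreme case at once. The powered comparison and the sample size stand.

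**What to change.** Replace the morning call with an order list generated once, in advance, with a recorded seed. Use permuted blocks of varying size, separately for the long COVID and control groups, aiming at about 22/22 in each, and reveal each entry only at the participant's first session. If the on-the-day call is kept, precede it with rng('shuffle') and log the generator state with each draw. State the chosen method in section 3.3.

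If recruitment has begun, tabulate realised order by group now and balance the remaining allocations.

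The cost is a few lines of code and one stored file, with no extra participants or visits. Blocked allocation is slightly more predictable than independent draws; varying the block size limits this.
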